Clinical deterioration will refer to worsening of anxiety, depressive symptoms, emotional instability, or psychosocial functioning identified through clinical evaluation, psychotherapy sessions, or validated clinical scales during follow-up. If deterioration is suspected, participants may undergo additional diagnostic evaluation using the Structured Clinical Interview for DSM-5-TR (SCID-5-TR) and other clinically relevant assessments.

Clinical Management:

Should symptoms arise requiring pharmacological treatment or additional psychiatric support, psychiatric consultation will be available within the Mental Health Unit of the same institution. Each case will be individually evaluated, and appropriate clinical measures may include extension of psychotherapy, referral to long-term psychotherapy, psychiatric treatment, or other clinically indicated interventions.

Withdrawal Criteria:

Participants may be withdrawn from the study in cases of severe clinical deterioration, serious adverse events, emergence of psychiatric conditions requiring immediate alternative treatment, participant request, non-adherence to study procedures, or investigator judgment that continuation may compromise participant safety or study integrity.

Protocol Deviations:

All protocol deviations, including missed sessions, incomplete assessments, deviations from intervention procedures, or unplanned clinical management modifications, will be documented and reviewed by the investigators. Any clinically relevant deviation affecting participant safety or trial conduct will be reported to the ethics committee when required.

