#### 2.10.2. Sample Size for Second Phase

The second phase of the clinical trial will require a larger sample size. Upon reaching 156 participants, the initial results comparing the two psychotherapies (experimental and active comparator groups) will be published. The research methodology will remain unchanged, but the second phase aims to assess the effect of condition across four distinct groups (BATF for depression, BATF for anxiety, control for depression, and control for anxiety).

An Analysis of Variance (ANOVA) will be employed for this comparison. The sample size calculation for this phase requires a total of 472 participants. Therefore, an additional 316 participants need to be recruited, with 79 participants in each of the four groups. This requirement accounts for the data from the initial 156 participants, which will be included in the evaluations for the second phase to achieve the total sample size of 472 for comparison across the four groups.

The sample size calculation for Phase 2 was based on a 2 × 2 factorial design with four equally sized groups, assuming balanced allocation across conditions (*n* = 118 per cell in the final sample). The calculation maintained the same statistical assumptions as Phase 1. No formal interim adjustments were planned, and the design assumes complete case availability at the final analysis stage. Importantly, no attrition (dropout) rate was included in the sample size calculation, which may result in reduced effective statistical power if loss to follow-up occurs during the trial.

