### 2.11. Statistical Methods

The primary analysis (Phase 1) will compare BATF versus Brief Focal Psychotherapy in a combined sample of participants with anxiety and/or depressive symptoms, irrespective of diagnostic category (“collapsed” clinical conditions). This analysis represents the primary confirmatory comparison of the trial.

Exploratory subgroup analyses within Phase 1 are pre-specified and will evaluate treatment effects separately in participants with anxiety and depressive symptoms.

The secondary analysis (Phase 2) will examine a pre-specified 2 × 2 factorial analytical framework (intervention × clinical condition), allowing assessment of main and interaction effects across four groups (BATF-depression, BATF-anxiety, control-depression, and control-anxiety), resulting in four analytical cells for the 2 × 2 factorial analysis.

For Phase 1, the primary comparison between BATF and Brief Focal Psychotherapy will be performed using Student’s *t*-test for normally distributed change scores or the Mann–Whitney U test when normality assumptions are not met. The first phase will include 156 participants.

Phase 2 will include a total sample of 472 participants (including participants from Phase 1 plus additional recruited participants). Change scores will be compared across the four predefined groups (BATF-depression, BATF-anxiety, control-depression, and control-anxiety) using one-way analysis of variance (ANOVA) or the Kruskal–Wallis test, as appropriate.

Assessments performed at Week 4 will be used to describe intermediate clinical evolution and may support exploratory analyses of treatment trajectories.

Effect Size Measure: Omega squared (ω^2^); Statistical Significance Level: α = 0.05.

Multiplicity for the co-primary outcomes will be controlled using the Holm–Bonferroni procedure. Secondary and subgroup analyses will be considered exploratory and interpreted accordingly. Exploratory biomarker analyses will apply false discovery rate (FDR) correction according to the Benjamini–Hochberg method.

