Primary Analysis: Recruitment will be continuous, and allocation will follow a pre-generated 1:1 randomization sequence, stratified by clinical condition. Participants will be enrolled until the target sample size of randomized participants is reached. All analyses will follow the intention-to-treat principle. Missing outcome data will be handled primarily using maximum likelihood estimation within mixed-effects models. Multiple imputation may be performed as a sensitivity analysis, when appropriate, to evaluate the robustness of the findings.

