#### Additional Analyses (Subgroup and Sensitivity)

As a sensitivity analysis, repeated-measures mixed-effects models may be conducted to evaluate the consistency of results across all assessment time points (baseline, Week 4, and Week 13), accounting for within-participant correlation.

Additional sensitivity analyses may include per-protocol analyses restricted to participants who complete the planned intervention and adjusted models controlling for baseline symptom severity, concomitant medication use, and treatment adherence (e.g., number of sessions attended), when appropriate. Post hoc exploratory analyses may be conducted as hypothesis-generating analyses if unanticipated patterns emerge.

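### Section 2.11 names a primary test that cannot use its own primary missing-data method, so it is unclear which analysis governs

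*Protocol article*

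**What the plan says.** All references are to the protocol article.

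- **Endpoint (2.5):** change in symptom severity from Week 0 to Week 13. Each participant is rated only on the scale for the primary diagnosis, MADRS for depression or HAM-A for anxiety.
- **Phase 1 primary test (2.11):** Student's t-test "for normally distributed change scores or the Mann–Whitney U test when normality assumptions are not met".
- **Phase 2 test (2.11):** one-way ANOVA or Kruskal–Wallis, also on change scores.
- **Population (2.11, under Primary Analysis):** "All analyses will follow the intention-to-treat principle". Section 2.8 adds that dropouts stay in that analysis, with unspecified methods for their missing data.
- **Missing data (same paragraph of 2.11):** "Missing outcome data will be handled primarily using maximum likelihood estimation within mixed-effects models". On imputation: "Multiple imputation may be performed as a sensitivity analysis, when appropriate, to evaluate the robustness of the findings".
- **Mixed model (Additional Analyses):** "As a sensitivity analysis, repeated-measures mixed-effects models may be conducted to evaluate the consistency of results across all assessment time points".
- **Week 4 scores (2.11):** descriptive, with possible exploratory use.
- **Withdrawal (2.4):** "Participants may be withdrawn from the study in cases of severe clinical deterioration, serious adverse events", among other reasons that include non-adherence and participant request. The section does not say whether scales are still collected afterwards.

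**The concern.** A missing-data method has to belong to the analysis it serves. Here the method called primary sits inside a model that the plan need not fit. The test that produces the confirmatory result has no method attached.

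Two things are at stake. First, the stated intention-to-treat rule cannot be met by the named test once any Week 13 score is missing. Second, two analysts following section 2.11 could report different primary estimates, and the choice between them could be made after the data are seen. If dropout depends on outcome in different ways in the two arms, those estimates can differ materially.

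**Working it through.** **1. What the named test needs.** For participant i the outcome is D_i = Y_i(Week 13) − Y_i(Week 0). The t-test compares the arm means of D, and Mann–Whitney ranks D. Without a Week 13 score D_i does not exist, and neither test has a likelihood step that could use the baseline and Week 4 scores instead. ANOVA and Kruskal–Wallis on D behave the same way.

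**2. Which test the trial was sized for.** Inputs from 2.10: difference 5, SD 11, two-sided α 0.05, power 80%, 1:1 allocation.

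- Normal approximation: n per arm = 2 × (1.960 + 0.842)² × 11² / 5² = 2 × 7.85 × 4.84 ≈ 76.
- Noncentral t: 77 per arm, power 0.800.

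This reproduces the stated 77 in 2.10.1. The two-sample t-test is therefore the calculation behind Phase 1, and no mixed model entered it.

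**3. The statements side by side.**

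| Element | Role given in the article | Can it use a participant with no Week 13 score? |
|---|---|---|
| t-test / Mann–Whitney on change | Primary, Phase 1 | No |
| ANOVA / Kruskal–Wallis on change | Phase 2 analysis | No |
| Maximum likelihood in mixed models | Primary missing-data method | Yes |
| Repeated-measures mixed model | Optional sensitivity analysis | Yes |
| Multiple imputation | Optional sensitivity analysis | Yes |

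No sentence links either of the methods that could use such a participant to the primary test.

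**4. Direction and size of bias (assumed inputs).** Let m be the share of an arm without Week 13 data, and δ the mean change of non-completers minus that of completers. The mean of the whole arm is the completers' mean plus m × δ. The complete-case contrast is therefore off by the difference between arms in m × δ.

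- Equal m and equal δ in both arms: bias 0.
- Assumed m of 10% and 30%, δ of 3 to 6 points in both arms: (0.30 − 0.10) × 3 = 0.6, and × 6 = 1.2 points. Against the 5-point target this is 0.6/5 = 12% to 1.2/5 = 24%.

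**5. Illustrative simulation (assumed inputs).** Settings: 2,000 runs; 78 per arm; one scale; true Week 13 difference -5 (BATF minus comparator); change SDs 9 at Week 4 and 11 at Week 13; correlation 0.6; all Week 4 scores observed. Dropout probability is 20% at the arm's mean Week 4 change and depends on Week 4 change as shown. The likelihood estimate adjusts the completers' mean by the regression of Week 13 on Week 4 change.

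| Who tends to drop out | Complete-case | Maximum likelihood |
|---|---|---|
| Unrelated to Week 4 change, both arms | -4.99 | -5.00 |
| Less improved, both arms | -4.99 | -4.98 |
| Less improved in BATF; unrelated in comparator | -6.36 | -5.03 |
| More improved in BATF; unrelated in comparator | -3.67 | -5.02 |
| More improved in BATF; less improved in comparator | -2.26 | -4.96 |
| Less improved in BATF; more improved in comparator | -7.73 | -5.00 |

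Dropout here depends only on an observed score, which is the setting where maximum likelihood is valid. The table shows that the two readings of the plan can part company. It does not predict by how much.

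**The case against.** **A statistical analysis plan is registered and may say which method governs.** It may. The clash is nevertheless between statements in one section of the article, so it is not detail left to another document.

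**The article never says that the primary analysis is complete-case.** This stands. A reader might infer that everyone without Week 13 data will certainly be dropped, but sections 2.8 and 2.11 state the opposite intention. The text also allows a reading in which the likelihood model takes over when data are missing. What can be said is that complete-case is the default result of the tests as named. The complete-data remark in 2.10.2 does not settle it, because it is a sample-size assumption for Phase 2.

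**The withdrawal criteria do not show that missing values will be poor outcomes.** This also stands. A reader might infer it from the references to deterioration and serious adverse events. The list also covers participant request and investigator judgment, withdrawal is permitted rather than required, and 2.4 does not say that assessment stops.

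**Unequal retention is not documented.** Correct. The arms differ in session number (at most three against at most ten), but both share the Week 13 assessment, and attending sessions is not the same as attending assessments. Differential dropout is possible but not shown.

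**Loss of power from attrition is already disclosed** in 2.10.2 and the Discussion. It is a separate matter and forms no part of this point.

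**A single mixed model of all participants would be wrong too.** Agreed. Each participant has only MADRS or only HAM-A, and a stratum term does not make a point on one scale equal a point on the other. The fix has to respect this.

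**Conclusion.** The contradiction is real. Section 2.11 pairs a primary test that needs a Week 13 score with a primary missing-data method belonging to a model that the plan makes optional. As written, the test and the missing-data rule cannot both be carried out. Run as named, the primary test would by default be complete-case, which is an inference from the tests chosen. Phase 2 has the same problem.

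The size of any bias cannot be derived, because the article gives no dropout figures. It is nil if dropout works alike in both arms. Under the assumed inputs above it reaches 0.6 to 1.2 points in the simple arithmetic and about 2.7 points in either direction in the most extreme simulated cases (5 − 2.26 = 2.74; 7.73 − 5 = 2.73). Those figures rest on assumed dropout patterns, a single scale and a mechanism that depends on Week 4 scores alone.

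**What to change.** Name one governing primary analysis and bring the three parts of section 2.11 (primary test, missing data, sensitivity analyses) into line with it.

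- **Preferred:** a likelihood-based repeated-measures model of Weeks 0, 4 and 13, with the treatment contrast at Week 13 as the primary estimate. Fit it separately for MADRS in the depression stratum and HAM-A in the anxiety stratum, or on a stated common standardised metric. Make the change-score test a sensitivity analysis.
- **Alternative:** keep the change-score test as primary and pre-specify multiple imputation that uses Week 4 scores as its primary missing-data method.

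Make the matching choice for the Phase 2 analysis.

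In the withdrawal paragraph of section 2.4, state that Week 4 and Week 13 scales are still collected after the study intervention stops, unless consent is withdrawn. This concerns data collection only and changes no clinical decision to stop.

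**Cost:** wording in the protocol, and in the analysis plan where needed, plus some assessor time for assessments after treatment stops. Both options rely on a missing-at-random assumption, and participants lost before Week 4 add no post-baseline information. Recruitment is anticipated from the fourth quarter of 2026, so the change can be made before any data exist.

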### 2.10. Sample Size

The standard deviation for the Montgomery-Åsberg Depression Rating Scale (MADRS) was estimated to be 11 [36]. The minimal clinically significant difference on the Montgomery-Åsberg Depression Rating Scale (MADRS) is considered to be 5 points. The minimal clinically important difference for the MADRS is not universally established and varies according to the estimation method and study population. Published estimates generally range from approximately 3 to 9 points, with values around 3–6 points considered among the most plausible across different methodological approaches. Therefore, a 5-point difference was adopted as a pragmatic mid-range estimate for sample size calculation purposes [37]. Alpha (α): a classical significance level of 5% is used, commonly applied in health research. A statistical power of 80% (β = 0.20) was adopted, as commonly recommended in health research.

The sample size was calculated based on the change in Montgomery–Åsberg Depression Rating Scale (MADRS) scores from baseline to week 13 (primary outcome). A two-sided significance level of 5% (α = 0.05), statistical power of 80% (β = 0.20), a clinically meaningful difference of 5 points, a standard deviation of 11, and a 1:1 allocation ratio were assumed. The calculation was performed using a two-sample *t*-test for independent means implemented in G*Power version 3.1.9.7. This corresponds to a standardized effect size of Cohen’s d = 0.45.

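### The missing-data robustness check, optional multiple imputation, in its standard form assumes missing at random just as the likelihood method does, so it cannot reveal informative loss.

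*Protocol article*

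**What the plan says.** The protocol article, section 2.11 (Primary Analysis paragraph), sets the principle "All analyses will follow the intention-to-treat principle" and then the method: "Missing outcome data will be handled primarily using maximum likelihood estimation within mixed-effects models". The next sentence gives the check on that method: "Multiple imputation may be performed as a sensitivity analysis, when appropriate, to evaluate the robustness of the findings". It lists no imputation variables and no shift, reference-based or pattern-mixture variant.

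The section on additional analyses lists three further options, all worded as possibilities:
- a repeated-measures model: "repeated-measures mixed-effects models may be conducted to evaluate the consistency of results across all assessment time points";
- per-protocol and covariate-adjusted models: "Additional sensitivity analyses may include per-protocol analyses restricted to participants who complete the planned intervention and adjusted models".

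None of these is described as varying the assumption about missing data.

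Two other statements bear on the point. Section 2.4 says: "Participants may be withdrawn from the study in cases of severe clinical deterioration, serious adverse events". And section 2.11 makes the Phase 1 primary test "Student’s *t*-test for normally distributed change scores or the Mann–Whitney U test when normality assumptions are not met", which is not a mixed model.

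**The concern.** A sensitivity analysis for missing data is useful when it changes the assumption that cannot be checked from the data. Likelihood-based mixed models and standard multiple imputation both assume that, given what was observed, those lost would have scored like those who stayed. With the same variables they estimate nearly the same quantity.

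This trial has a foreseeable route to a breach of that assumption. Outcomes are measured only at baseline, Week 4 and Week 13. A participant who deteriorates after Week 4 and is withdrawn leaves no score that shows the deterioration. Contact also differs by arm: no BATF session is scheduled between Weeks 4 and 13, while the comparator allows up to ten weekly sessions. Loss, or the detection of deterioration, could therefore differ between arms.

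If the two analyses agreed, the report could call the result robust although the assumption that matters had not been varied. A spurious or masked treatment difference caused by informative loss would go unnoticed.

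**Working it through.** **Inputs from the article.** Section 2.10: SD 11, target difference 5 points, two-sided α 0.05, 80% power, 1:1 allocation. Section 2.10.1: 77 per group required, raised to 78. Section 2.10.2: no attrition allowance; 118 per cell finally and 79 per cell added in Phase 2.

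**Inputs assumed.** The dropout rates and the unobserved shifts. The article gives neither.

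**1. The plan's own figure.** With d = 5/11, the noncentral t distribution gives power 0.8003 at 77 per arm and 0.805 at 78. The stated 77 is reproduced.

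**2. Does multiple imputation detect informative loss?** This was simulated with 78 per arm and a true difference of 0. Scores at the three visits were normal, with an SD of change of about 10.9. There were 1,500 replicates and 30 imputations. Comparator loss was random at 20%. BATF loss depended on the Week 13 score to a varying degree.

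| BATF loss | Overall missing | Likelihood | Multiple imputation |
|---|---|---|---|
| ignorable | 18% | −0.03 | −0.03 |
| moderately informative | 20% | −1.07 | −1.07 |
| strongly informative | 24% | −2.32 | −2.32 |

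Negative values favour BATF. The two estimates correlate above 0.997 and differ by about 0.1 point per trial. Imputation reproduces the bias of the likelihood analysis and does not expose it.

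**3. Size of the bias.** Bias = share missing in one arm × shift beyond the missing-at-random prediction. At 10% missing and a 2-point shift it is 0.10 × 2 = 0.2 points. At 30% and 8 points it is 0.30 × 8 = 2.4 points. That is 4% to 48% of the 5-point target.

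**4. Tipping shift for an observed 5-point difference, 78 per arm on one scale.** Let m be the share missing per arm, n = 78(1 − m) and SE = 11√(2/n). The critical difference is t(0.975, 2n − 2) × SE. The tipping shift, applied to BATF only, is (5 − critical difference)/m.

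| m | n per arm | SE | Critical difference | Tipping shift |
|---|---|---|---|---|
| 15% | 66.3 | 1.91 | 3.78 | 8.1 |
| 20% | 62.4 | 1.97 | 3.90 | 5.5 |
| 25% | 58.5 | 2.03 | 4.03 | 3.9 |

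The SE treats only observed participants as informative and is held fixed under the shift, which is a simplification.

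**5. False-positive rate with unequal loss.** Assume 10% loss in one arm and 30% in the other, with lost participants worse by δ in both arms. SE = 11√(1/70.2 + 1/54.6) = 1.98 and bias = δ(0.30 − 0.10). For δ = 5 the bias is 1.0 and the null is rejected 8.0% of the time. For δ = 8 the bias is 1.6 and the rate is 12.7%. The nominal rate is 5%.

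**6. Where step 4 does not apply.** Section 2.5 defines the co-primary outcomes within each diagnostic stratum. Section 2.10.2 implies 118 − 79 = 39 per cell in Phase 1. With 20% missing, n = 31.2, SE = 11√(2/31.2) = 2.79 and the critical difference is 2.00 × 2.79 ≈ 5.6. An observed 5-point difference is then not significant, so there is no tipping shift.

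**The case against.** The strongest reply is that this is detail for the analysis plan, which section 2.1 says is available in the registry. The article never writes missing at random. Multiple imputation is also the usual vehicle for delta-adjusted analyses, and auxiliary variables could make it differ from likelihood. This limits the point to standard multiple imputation and to the text shown. It does not remove it, because the article itself names the method and gives it the task of testing robustness, without any feature that would let it test the missing-data assumption.

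A second reply is that likelihood may not be the main analysis at all. The t-test or Mann–Whitney test in section 2.11 would, as written, drop participants without a Week 13 score, and the mixed model reappears later as a sensitivity analysis. Against a complete-case test, imputation does change the assumption, since it can condition on Week 4. That stands, and the passages need reconciling. But imputation under missing at random would still not address informative loss.

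Three stronger readings are tempting and are not supported:
- A reader might infer that no listed analysis lets missing participants do worse than observed ones. Both methods predict worse Week 13 scores for people who were worse at Week 4. What is absent is any departure from that prediction.
- A reader might infer that deteriorating participants are removed. The article says they may be withdrawn, offers other management, and keeps dropouts in the intention-to-treat analysis. Withdrawal driven by a recorded Week 4 score is compatible with missing at random.
- A reader might infer that loss will differ by arm. The contact schedules differ, but both arms share the Week 4 and Week 13 assessments, so differential loss is a possibility only.

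**Conclusion.** The point holds in this form: the one analysis named as the check on missing-data handling shares, in its standard form, the assumption it would need to vary, and the other listed analyses do not vary it either. This follows from the methods named and needs no figure.

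The size is illustrative. The 5.5-point tipping shift rests on an assumed 20% loss per arm, a pooled analysis of 78 per arm on one scale with SD 11, a shift in BATF only, and no Holm correction. The false-positive rates of 8.0% to 12.7% rest on assumed loss of 10% versus 30% and assumed shifts of 5 to 8 points. A reader might take these as properties of the trial. The article does not support that: it gives no dropout rate, its co-primary outcomes are within strata, and at 39 per arm no significant 5-point result exists to tip. What the figures do show is that a shift of about the size of the trial's own target difference can be enough to matter in the pooled case. Nor does the article show that any such bias will occur.

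**What to change.** Replace the multiple-imputation sentence in section 2.11 with a mandatory, prespecified analysis, for example:

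*Robustness to the missing-at-random assumption will be examined by delta-adjusted multiple imputation of Week 13 change. The imputed values will be worsened over a prespecified range of shifts, varied independently in each arm, and the combinations at which the primary conclusion changes will be reported.*

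Set the range separately for MADRS and HAM-A, because a point does not mean the same on both. For the collapsed comparison, express the shift in SD units. First reconcile the statements in section 2.11 and the additional-analyses section on whether the primary analysis is a test on change scores or a mixed model, and apply the tipping-point analysis to whichever is kept.

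Standard multiple imputation may stay as a check on modelling choices, but should not be presented as testing robustness to the missing-data assumption. If the registered analysis plan already contains such an analysis, the article need only say so.

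The cost is wording and slightly more analysis work. No extra participants or data are needed, and since section 2.2 anticipates recruitment from the fourth quarter of 2026, the change can be made before data exist.
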